### Data analysis

All statistical analyses will be undertaken using relevant statistical software. Descriptive statistics (mean and standard deviation (SD) or median and range when non-normal) will be generated for all assessed outcomes. For acceptability, feasibility, appropriates and usefulness, individual scores from each item will be summed (reverse scored where necessary) and combined to provide a score for each community. A score of ≤2 will be considered a negative response, indicating the Action-RESPOND program is considered unacceptable, while ≥4 will be indicative of an acceptable program. For feasibility, ≥4 (higher scores) will indicate greater feasibility, while ≤2 (lower scores) will indicate lower feasibility, consistent the recommendations of Weiner et al (2017) in the Feasibility of Intervention Measure [52]. Answers to the open-ended questions will be analysed qualitatively.

For implementation outcomes (fidelity and adoption of the selected action for implementation), item responses will be summed to provide an overall fidelity and an overall adoption score for both the intervention and control group. This will be compared between groups using a linear regression, controlling for baseline scores. Changes in implementation determinants and adaptations to actions will be described narratively for each community.

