*Delivery modality*. Action-RESPOND consist of seven implementation strategies that will be delivered over approximately 9-months via one online meeting (GMB3 debrief), one face-to-face group education workshop (Edu Workshop), two formal facilitation contacts delivered by an implementation coach (Check-in sessions) and local tailored support as requested. Additionally, we will incorporate system science concepts, including qualitative systems mapping, use of reference modes (which capture the dynamic nature of key factors within a system) and feedback loops, during the delivery of the multicomponent implementation strategy (see Table 1). The research team delivering the intervention consists of systems science experts (AB, JH) and implementation scientists (SY, [name]) and an Implementation Coach (MH). The Implementation Coach (MH) has 10 years of health promotion experience working within the targeted communities and is situated within one community of the Ovens-Murray region.

The Edu Workshop will be delivered face-to-face to the ‘backbone team’ who consist of community development workers from local councils, health promotion practitioners from relevant health services and relevant non-government organisations in the region. This session will be co-facilitated by systems science (AB) and implementation science (SY) experts together with the Implementation Coach (MH).

The Implementation Coach (MH) will be primarily responsible for delivering the two facilitation check-in sessions. The sessions will either be delivered over videoconference call or face-to-face (depending on preference of community) with identified Implementation Champion(s) within each community. The Champion/s are likely to consist of one or multiple individuals (in the instance of shared role or part-time staff) who are health promotion officers within the local community health teams or local council.

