### Appropriateness and usefulness of the implementation strategies

At follow-up, the appropriateness of the implementation strategies will be assessed with intervention communities via four items on a Likert-scale (1 = strongly disagree to 5 = strongly agree) and one open-ended item. The backbone team members will also be asked to report on how useful they thought each of the individual implementation strategies were (Likert scale, with 1 = not helpful at all to 5 = extremely helpful) and to qualitatively report on why they rated the components this way.

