### Progression criteria

The advisory group for this research will assess suitability for progression to a fully powered trial in similar communities in Victoria, using data collected related to fidelity, adoption, and acceptability of the implementation strategies via this study as well as systematic reviews of systems-based obesity prevention interventions on the potential benefits on child outcomes. Together this data will allow for assessment on the potential for a larger trial focused on implementation specifically. These decisions will be made via majority, by core members of the research team, including a representative from participating communities. Specifically, the team must rate the program as sufficiently acceptable and feasible for it to be likely adopted by over half of the communities in which it was offered. Alternatively, the team may decide that this could be reasonably expected with adaptations to the program, based on steps previously employed. Further, the data collected will be used to identify opportunities to strengthen the intervention and refine trial methods prior to a fully powered implementation trial.

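### Usefulness is rated strategy by strategy, but the only quantitative score specified for it is a sum per community, which cannot tell the strategies apart

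*Protocol article*

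**What the plan says.** Three places in the protocol article bear on this.

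- **Appropriateness and usefulness of the implementation strategies.** At follow-up, members of the intervention communities' backbone teams are asked to "report on how useful they thought each of the individual implementation strategies were". Each rating runs from 1 to 5, higher meaning more helpful, and an open-ended answer gives the reasons behind the ratings. The unit being rated is the single strategy.
- **Data analysis.** One sentence sets the scoring for four outcomes together: "For acceptability, feasibility, appropriates and usefulness, individual scores from each item will be summed", with reverse scoring where needed, and "combined to provide a score for each community". Usefulness is named in it. The same section promises descriptive statistics for every assessed outcome and qualitative analysis of open-ended answers. It states no quantitative summary by strategy.
- **Progression criteria.** Besides the decision on progression, "the data collected will be used to identify opportunities to strengthen the intervention and refine trial methods" before a fully powered trial.

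The delivery modality text within the section on the multicomponent implementation strategy gives the size of the package: "Action-RESPOND consist of seven implementation strategies".

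**The concern.** Adding items makes sense when they are several readings of one construct, as with the three fidelity items. The usefulness items are ratings of different things: evidence briefs, prioritisation support, feedback to the community, champions, training, tailored facilitation and leadership engagement. What such a question can show is the contrast between those parts, and a total over items removes that contrast.

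The stake is the refinement aim. To strengthen a seven-part package one needs to know which parts were found helpful. The article describes no other rating that it says is asked strategy by strategy; the acceptability items concern Action-RESPOND as a whole. If the stated rule is followed and nothing is added, these ratings enter the results as one package-level number per community. A later choice of which strategies to highlight would then be made after seeing the data.

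**Working it through.** The plan states no figure of its own to reproduce. The check is whether the specified score keeps any information about individual strategies.

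**Inputs**

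- Scale: 1 to 5 per item (usefulness section).
- Number of items: 7. This is an assumption of one item per strategy; the article states seven strategies but not the item count.
- Score: sum over items, then combined to one value per community (Data analysis).
- Members per community: 3 to 8. This is stated for acceptability and assumed to apply to usefulness as well.

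**Step 1: two opposite profiles, one total**

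- Profile A: 5+5+5+2+2+2+2 = 23, mean 23/7 = 3.29.
- Profile B: 3+3+4+3+3+4+3 = 23, mean 23/7 = 3.29.

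A has three strategies at the top of the scale and four near the bottom. B is almost flat. The score is the same.

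**Step 2: how general this is**

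- Possible profiles for one respondent: 5^7 = 78,125.
- Possible totals: from 7×1 = 7 to 7×5 = 35, that is 35 − 7 + 1 = 29.
- Enumeration of all profiles finds 1,520 with a total of 28 (mean 28/7 = 4.0). Of these, 1,127 contain at least one strategy rated 2 or lower: 1,127/1,520 = 74%.
- For example, 5,5,5,5,5,2,1 and 1,2,5,5,5,5,5 and 4,4,4,4,4,4,4 all total 28. The first two rank the strategies in opposite order, and the third does not rank them at all.

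The mark of 2 is used here only to mean a low point on the scale. The 74% is a share of possible profiles, not a forecast of what respondents will answer.

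**Step 3: combining members does not recover the contrast**

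If three members of a community all answer as A, their combined total is 3×23 = 69 and their average is 23. Three members answering as B give the same 69 and 23.

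**Step 4: what the alternative yields**

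Averaging members within a community for each strategy gives 7 values per community, or 7×5 = 35 values over the five intervention communities, and so 7 per-strategy summaries. The reporting unit remains the local government area, as the Data management section requires.

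**The case against.** The strongest reply is that the plan keeps a strategy-specific source. Reasons for the component ratings are collected and will be analysed qualitatively. The promise of descriptive statistics for all outcomes could also cover per-strategy figures, and nothing says the sum replaces them. This stands. A reader might infer that the trial will be unable to show which strategies to keep or change; the article does not support that. The limit applies to the specified score. Reasons are still easier to interpret beside the distribution of ratings they explain, and the text does not promise that distribution.

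The scoring sentence covers four outcomes and does not say whether summation runs over items, over members or both. Summing over items is the natural reading, though combining members item by item is not ruled out. If that is what is meant for usefulness, the sentence should say so.

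Three further inferences should be resisted.

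- The ≤2 and ≥4 cut-offs might be read as marking a single strategy as negative or good. The article attaches them to acceptability of the program and to feasibility, and defines none for the usefulness of one strategy.
- The usefulness total might be thought to duplicate acceptability. No acceptability item asks about helpfulness.
- The progression decision might be thought to turn on the usefulness score. That decision names fidelity, adoption and acceptability, with a feasibility judgement. Refinement draws on the collected data generally, including the structured check-in records on barriers, adaptations and action progress.

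Finally, every sum loses item detail, and an article condenses a longer protocol. The point does not rest on an omission, however. Usefulness is expressly placed under a rule that does not suit the way it is measured.

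**Conclusion.** The point holds in limited form. Usefulness is measured per strategy, while the only quantitative score specified for it is a sum per community that cannot separate the strategies. Under the one-item-per-strategy assumption, 78,125 profiles map to 29 totals, and clearly different profiles share the total of 23. A different item count would change these figures but not the conclusion, provided there is more than one item.

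What is affected is how directly the pilot serves its refinement aim, for which the qualitative answers are left as the only planned strategy-specific source. The between-group comparison of fidelity and adoption is untouched, no test or decision rule is tied to the usefulness score, and the item ratings should still be available. This is a worthwhile improvement at almost no cost, not a threat to the trial's validity.

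**What to change.** Remove usefulness from the summed-score sentence in Data analysis, or keep its sum only as a supplement. Add a sentence along these lines: *Usefulness will be summarised separately for each implementation strategy; members' ratings will be averaged within each intervention community, and the mean or median and range of the five community values will be reported per strategy, beside the qualitative reasons for the ratings.*

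Do not apply the ≤2 and ≥4 cut-offs to single strategies unless they are first defined for that use. Keep summing for items that measure one construct.

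The cost is one sentence and one table, using data already planned.

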### Acceptability of implementation strategies

All backbone team members of intervention communities (between 3–8 in each community) will be asked to report on the acceptability of the intervention at follow-up. Acceptability will be defined as the perception amongst the backbone team that the intervention and implementation strategies are agreeable, palatable or satisfactory [51]. This will be assessed using seven items on a five-point Likert scale reporting on the following elements of Action-RESPOND:

Affective attitude (1 = strongly dislike to 5 = strongly like),Burden (1 = no effort at all to 5 = huge effort),Perceived effectiveness (1 = strongly disagree to 5 = strongly agree),Intervention coherence (1 = strongly disagree to 5 = strongly agree),Self-efficacy (1 = not at all confident to 5 = very confident),Opportunity costs (1 = did not have to give up activities to 5 = gave up many activities), andOverall acceptability (1 = completely unacceptable to 5 = completely acceptable).These items are underpinned by the Theoretical Framework of Acceptability [51], a validated framework used to assess the acceptability of healthcare interventions from the perspectives of intervention deliverers and recipients.

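### Item scores are summed but judged against cut-offs of 2 and 4 that only fit a 1–5 mean, so the acceptability rule cannot return a negative result

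*Protocol article*

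**What the plan says.** The Data analysis section gives one scoring rule for acceptability, feasibility, appropriateness and usefulness: "individual scores from each item will be summed (reverse scored where necessary) and combined to provide a score for each community". The cut-offs follow at once. At the lower end: "A score of ≤2 will be considered a negative response, indicating the Action-RESPOND program is considered unacceptable". At the upper end, a score of 4 or more counts in the program's favour. Feasibility has the same thresholds: "For feasibility, ≥4 (higher scores) will indicate greater feasibility, while ≤2 (lower scores) will indicate lower feasibility".

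The outcome sections fix the scales. For acceptability: "This will be assessed using seven items on a five-point Likert scale". Appropriateness is measured "via four items on a Likert-scale", each item running from 1 to 5. Usefulness is one 1–5 rating for each implementation strategy, and the Delivery modality text counts seven strategies. Raters are the backbone team members of the intervention communities, 3 to 8 in each.

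Nowhere does the article say that a sum is divided by the number of items, and it does not define how scores are combined into a community score.

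**The concern.** Thresholds of 2 and 4 make sense on a scale from 1 to 5, where they mark the second-lowest and second-highest response options. A sum of several 1–5 items is on a longer scale that starts at the number of items. With seven items the lowest possible sum is already above the threshold for a positive verdict, so the rule would call the program acceptable whatever the communities answered.

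Assessing acceptability and feasibility is one of the aims listed in the Introduction. The Progression criteria section names acceptability data among the inputs to the decision on a fully powered trial, and requires the team to judge the program acceptable and feasible enough. The cut-offs of 2 and 4 are the only numerical standard for acceptability in the article. A standard that cannot be failed tells the decision makers nothing.

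There is a second problem. If combining means adding over respondents, the community score also depends on team size, so communities giving identical ratings would get different scores.

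**Working it through.** **Inputs**

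| Quantity | Value | Where |
|---|---|---|
| Acceptability items | 7, each 1–5 | Acceptability of implementation strategies |
| Appropriateness items | 4, each 1–5 | Appropriateness and usefulness of the implementation strategies |
| Usefulness ratings | 1–5 per strategy, 7 strategies | same section; Delivery modality |
| Feasibility items | number not given | – |
| Raters per community | 3–8 | Acceptability of implementation strategies |
| Cut-offs | ≤2 negative, ≥4 positive | Data analysis |

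**Step 1: range of a sum.** With k items scored 1 to 5, the sum runs from k to 5k. Reverse scoring replaces x by 6 − x, which is again 1 to 5, so the range does not change.

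- Acceptability: 7 × 1 = 7 to 7 × 5 = 35.
- Appropriateness: 4 × 1 = 4 to 4 × 5 = 20.
- Usefulness over seven strategies: 7 to 35.

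**Step 2: apply the stated cut-offs to the sum.** Every possible response pattern of one respondent was enumerated.

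| Scale | Patterns | Sum ≤2 | Between 2 and 4 | Sum ≥4 |
|---|---|---|---|---|
| Acceptability | 5^7 = 78,125 | 0 | 0 | 78,125 |
| Appropriateness | 5^4 = 625 | 0 | 0 | 625 |
| Usefulness | 5^7 = 78,125 | 0 | 0 | 78,125 |

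**Step 3: combine over respondents.** Averaging members' sums leaves the acceptability range at 7 to 35, so nothing changes. Adding them gives:

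- three members: 3 × 7 = 21 to 3 × 35 = 105;
- eight members: 8 × 7 = 56 to 8 × 35 = 280.

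On that reading, eight members giving the worst answers (56) outscore three members answering 2 throughout (3 × 14 = 42).

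**Step 4: apply the same cut-offs to the item mean.** The mean runs from 1 to 5.

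| Scale | Mean ≤2 | Between 2 and 4 | Mean ≥4 |
|---|---|---|---|
| Acceptability | 3,180 | 71,765 | 3,180 |
| Appropriateness | 70 | 485 | 70 |

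These are counts of possible patterns, not probabilities. They show that on the mean all three outcomes can occur. The equivalent cut-offs on a respondent's sum are 2k and 4k: ≤14 and ≥28 for seven items, ≤8 and ≥16 for four.

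**Step 5: feasibility.** The item count has to be assumed. With one or two items a sum of 2 or less is possible; with three the minimum is 3; with four or more every sum is at least 4. The result for feasibility therefore depends on a number the article does not give.

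**The case against.** The best defence is that this is a slip of wording. The word for combining scores is undefined and could include averaging, thresholds of 2 and 4 point to a 1–5 scale, and an analyst who saw a lowest possible total of 7 would notice. That is probably what would happen. But the text says the items are summed, and the next paragraph uses the same word for fidelity and adoption, where a total is a workable score. Leaving the repair to the analyst also leaves it until the data are in hand, and different repairs can disagree. For example, a respondent who gives 4 on the overall acceptability item and 3 on the other six, after reverse scoring, has an item mean of (4 + 6 × 3)/7 = 3.14, which is neither verdict, but counts as acceptable on the single overall item.

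Three other points limit the reach of the finding:

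- **Progression.** The decision is a majority judgement that also draws on fidelity, adoption and systematic reviews, allows for adaptations, and does not cite the cut-offs. A wrong classification would inform it, not dictate it. Open-ended answers and usefulness ratings with reasons could still reveal a poorly received program.
- **Scope.** The sentences with the cut-offs name acceptability and feasibility. Applying them to appropriateness and usefulness is a reading of the paragraph, which scores all four together.
- **Recoverability.** The scores are descriptive, no between-group comparison depends on them, and item data are kept, so rescoring is always possible.

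These points limit the consequences. None makes the summed rule and its thresholds compatible.

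**Conclusion.** The point holds. Followed as written, the acceptability rule returns acceptable for 78,125 of 78,125 possible response patterns and unacceptable for none. The same holds for the four appropriateness items (625 of 625) and seven usefulness ratings if the cut-offs are meant to cover them. For acceptability the result rests only on the stated item count and response range, and it stands whether respondents' sums are averaged or added. The dependence on team size arises only if they are added. Nothing is claimed for feasibility, whose item count is not given. The effect on progression is indirect, but the error sits in a stated threshold for a main pilot outcome and should be corrected before the scores are analysed.

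**What to change.** In the Data analysis section, replace summing by averaging for acceptability, feasibility, appropriateness and usefulness. Suggested text: *For each respondent, the score is the mean of the items after reverse scoring where needed. The community score is the mean of its respondents' scores and lies between 1 and 5. A community score of 2 or less is negative, 4 or more is positive, and anything between is neither.*

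If totals are preferred, keep each respondent's sum, average the sums within the community, and rescale the cut-offs to ≤14 and ≥28 for seven items and ≤8 and ≥16 for four. Either version works; one must be chosen in advance. State which of the four outcomes the cut-offs apply to, and give the number of feasibility items.

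Sums can stay for fidelity and adoption, which are compared by regression without a cut-off. The cost is a sentence or two in the analysis section and, since the article says modifications will be recorded there, an update of the trial registration. No new data are required.

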### Progression criteria

The advisory group for this research will assess suitability for progression to a fully powered trial in similar communities in Victoria, using data collected related to fidelity, adoption, and acceptability of the implementation strategies via this study as well as systematic reviews of systems-based obesity prevention interventions on the potential benefits on child outcomes. Together this data will allow for assessment on the potential for a larger trial focused on implementation specifically. These decisions will be made via majority, by core members of the research team, including a representative from participating communities. Specifically, the team must rate the program as sufficiently acceptable and feasible for it to be likely adopted by over half of the communities in which it was offered. Alternatively, the team may decide that this could be reasonably expected with adaptations to the program, based on steps previously employed. Further, the data collected will be used to identify opportunities to strengthen the intervention and refine trial methods prior to a fully powered implementation trial.

### Trial discontinuation or modification

It is not anticipated that any events would occur that would warrant discontinuing the trial. Baseline data collection for Action-RESPOND has commenced, and the communities have been recruited to the RESPOND trial and continue to be engaged with the program. Any unforeseen adverse events will be reported to Deakin HREC (primary approval committee) and appropriate action taken to address the event. The trial registration record will be updated with any protocol modifications and any deviations from the original protocol will be reported when publishing trial outcomes.

